### Sample Size

An a priori power analysis was conducted in G*Power (version 3.1.9.7; Erdfelder, Faul, and Buchner) to estimate the sample size required to detect a small-to-medium longitudinal intervention effect in a group comparison. Consistent with common planning approaches for repeated-measures trials, the calculation targeted the group × time interaction under conservative assumptions and serves as an approximation for the primary longitudinal analyses. We assumed an effect size of *f*=0.20, *α*=.025 and statistical power=.95. The correlation among repeated measures was set to *r*=0.50 and the nonsphericity correction to *ε*=0.75 to account for plausible deviations from perfect sphericity. Under these assumptions, G*Power yielded a minimum required sample size of 114. To account for dropout, a target sample size of 200 was prespecified. This inflation reflects the increased risk of dropout in the TAU control group due to the 6-month waiting period and the typical loss to follow-up in digital health trials. The larger sample ensures robustness against assumption violations and maintains adequate power.

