### Statistical Analysis

All statistical analyses will be conducted using the statistical software R (version 4.5.0; R Core Team). For the PP analysis, “full adherence” will be defined a priori. Participants must complete at least 9 out of the 12 intervention modules (≥75% completion rate) within the intended 12-week intervention period to be included in the PP dataset. Thresholds such as completing ≥75% of modules are commonly reported in digital intervention research to operationalize adherence criteria, although empirical justification varies across studies, and this threshold is considered consistent with existing eHealth adherence frameworks [28]. Participants who complete fewer than 9 modules or who finish all modules in an implausibly condensed time frame that violates the intended weekly structure will be excluded from the PP dataset. First, all primary and secondary outcomes as well as participant demographics and baseline characteristics will be analyzed descriptively (means, SDs, and frequencies), both for the total sample and stratified by the study group (EGpsych, EGcomp, and TAU). To examine intervention effects, mixed models for repeated measures will be used as the primary analytic approach. The mixed models for repeated measures allow the inclusion of all available outcome data and accommodate unequal assessment schedules between groups due to the 6-month waiting period in the TAU condition. The primary randomized comparison will focus on the matched assessment approximately 6 months after baseline, corresponding to the 3-month follow-up in the experimental groups (T2) and the end of the waiting period in the TAU group (TAU-T1). For each primary and secondary outcome, models will include fixed effects for group (EGpsych vs EGcomp vs TAU), time (baseline vs matched 6-mo assessment), and the group × time interaction. A participant-specific random intercept will be included to account for within-person correlation. The group × time interaction will be used to test differential change between conditions. Holm-corrected post hoc contrasts will be applied for pairwise comparisons where applicable. If model assumptions are violated, appropriate robust methods will be considered. Outcome data collected in the TAU group after participants have received access to CHRONIC (eg, TAU-T2 and TAU-T3) will not be included in the primary randomized comparison because TAU no longer represents a control condition at that stage. Post-waitlist TAU data will instead be analyzed separately and within-group (exploratory) to describe changes following delayed program access. Exploratory analyses within each study arm will be reported descriptively. However, comparisons across nonmatched time intervals will not be interpreted as randomized sensitivity analyses. When a significant main or interaction effect is detected, Holm-corrected post hoc tests will be applied to determine the specific time points and group differences, while controlling for the family-wise error rate.

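### The primary group × time test is a change-score comparison: valid, but less precise than adjusting for the baseline the trial already collects (25% less variance at the plan's r=0.50)

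*Protocol article*

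**What the plan says.** The Statistical Analysis section sets out the primary model in full. The fixed effects are group (three arms), time (two levels: baseline and the matched 6-month assessment) and their interaction. On the covariance it says: "A participant-specific random intercept will be included to account for within-person correlation". On the test it says: "The group × time interaction will be used to test differential change between conditions". Holm-corrected pairwise contrasts follow.

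No part of the article enters baseline as a covariate or holds the baseline means equal across arms. Baseline pain severity appears only as a possible exploratory moderator. Missing values are to be handled by multiple imputation.

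The Sample Size section plans for the same test: "the calculation targeted the group × time interaction under conservative assumptions". Its inputs are "We assumed an effect size of *f*=0.20, *α*=.025 and statistical power=.95" and "The correlation among repeated measures was set to *r*=0.50 and the nonsphericity correction to *ε*=0.75", and the result is "G*Power yielded a minimum required sample size of 114". The target was then raised: "To account for dropout, a target sample size of 200 was prespecified".

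**The concern.** Baseline is measured before the program starts, so randomization makes the true baseline means equal in all three arms. The planned model nevertheless estimates a separate baseline mean for each arm and subtracts it. The noise in those baseline means then enters the treatment contrast at full weight, whereas regression on baseline would weight it by the actual correlation.

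What is at stake is precision, for all three primary outcomes and for every secondary outcome analysed with the same model. It matters most where the true difference is modest. The comparison of the two feedback formats may be such a case.

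**Working it through.** **Inputs.** From Sample Size: f=0.20, α=.025, power .95, r=0.50, ε=0.75, minimum N 114, target N 200. From Study Design and Statistical Analysis: three arms and two time levels in the primary model. Assumed here: equal allocation, and the same SD (σ) at both times.

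**1. The plan's own figure.** This uses the G*Power within-between interaction with k groups and m measurements:
- λ = f²·N·m·ε/(1−r)
- df1 = (k−1)(m−1)ε
- df2 = (N−k)(m−1)ε

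With k=3, m=3 and ε=0.75, the smallest N is 113, or 114 for equal arms. At N=114, λ = 0.04·114·3·0.75/0.5 = 20.52 and power is 0.954. The stated 114 reproduces.

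The primary model has only two time levels, where ε must be 1. That version needs N=115 (117 for equal arms), which is practically the same.

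**2. The interaction is a change-score contrast.** In simulated complete data with 67 per arm, the random-intercept interaction and its standard error matched the difference in mean change and its pooled standard error: 0.05327 against 0.05327, and 0.16786 against 0.16786.

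**3. Variance per participant.**
- Change score: 2(1−r)σ² = 2(0.5)σ² = 1.00σ²
- Baseline-adjusted: (1−r²)σ² = (1−0.25)σ² = 0.75σ²
- Ratio: (1−r²)/[2(1−r)] = (1+r)/2 = 0.75

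Over 20,000 simulated trials at r=0.50 the two variances were 0.0301 and 0.0227, a ratio of 0.753. The standard error falls by 1−√0.75 = 13%. Seen from the other side, the planned test carries 1/0.75 − 1 = 33% more variance.

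| r | Variance ratio | Reduction in SE |
|---|---|---|
| 0.3 | 0.65 | 19% |
| 0.5 | 0.75 | 13% |
| 0.7 | 0.85 | 8% |
| 0.8 | 0.90 | 5% |

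**4. Power at the plan's own effect size.** With two times and ε=1, λ = 0.04·N·2/0.5 = 0.16N for the planned test and 0.16N/0.75 after adjustment (df2 = N−3 and N−4).

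| N | Planned | Adjusted |
|---|---|---|
| 114 | 0.949 | 0.988 |
| 200 | 0.9987 | 0.9999 |

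The N needed for 95% power falls from 115 (117 for equal arms) to 87.

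**5. Power at smaller effects.** These effect patterns are assumptions; the article does not give them. For the omnibus test at α=.025, λ = (N/3)·Σ(μ−μ̄)²/v, with means in SD units, v=1.00 for change and v=0.75 adjusted. The sum of squares is 0.1667 for arm means 0, 0.5, 0.5 and 0.125 for 0, 0.25, 0.5.

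| Arm means (SD) | N | Planned | Adjusted |
|---|---|---|---|
| 0, 0.5, 0.5 | 114 | 48% | 63% |
| 0, 0.5, 0.5 | 200 | 78% | 90% |
| 0, 0.25, 0.5 | 114 | 36% | 48% |
| 0, 0.25, 0.5 | 200 | 63% | 78% |

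**6. Why steps 4 and 5 differ so much.** Setting 0.16N = (N/3)·(2/3)d² gives d² = 0.72, so d ≈ 0.85. In this convention, f=0.20 corresponds to about 0.85 SD when two arms share the whole effect.

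**The case against.** The strongest reply is that nothing in the plan is wrong. The interaction test is valid and unbiased, and the sample size was calculated for that same interaction, so plan and calculation agree. At f=0.20 and N=200, power exceeds 99.8% with either analysis. All of this stands.

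Three stronger readings are tempting, and the article supports none of them:

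- **That the planned test is biased or inflates the type I error.** It does neither. A chance baseline imbalance does shift the change-score estimate in a given trial, but over randomizations this averages out. It is the same phenomenon as the variance loss and must not be counted twice.
- **That this choice leaves the trial underpowered.** By the plan's own f=0.20 it does not. The lower power figures in step 5 depend on assumed arm patterns. Whether f=0.20 is a realistic target is a separate question.
- **That 25% is a fixed figure.** It depends on r, and "The correlation among repeated measures was set to *r*=0.50" is a planning input, not an estimate of the correlation between baseline and 6 months on these scales. At r=0.8 the variance saving is 10%.

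It can also be said that a change contrast answers the plan's question about differential change. Under randomization, however, both analyses estimate the same between-arm difference at 6 months; they differ in precision. Multiple imputation does not remove the gap, because the contrast fitted to the imputed data is still a difference in change.

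**Conclusion.** The point holds as a recommendation about efficiency. The article fixes a valid primary contrast that is less precise than one available from the same data, and no other section repairs this.

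Baseline adjustment would cut the variance of the effect by 25% at r=0.50, with a range from 35% at r=0.3 to 10% at r=0.8. At the planned effect size the practical gain is small: about 95% to 99% power at N=114, and next to nothing at N=200. It becomes material if true effects are smaller or if losses bring the analysed number towards 114.

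The figures assume equal variances at both times, equal allocation, and r=0.50 for the baseline-to-6-month pair. The identity with a change-score analysis is exact for complete or imputed data with a non-negative random-intercept variance, and approximate if the model is fitted to incomplete data.

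**What to change.** Before outcome data are seen, amend the Statistical Analysis section as follows:

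- Make the primary analysis of each outcome the 6-month score, with group as the factor and the baseline value of the same outcome as a covariate. Alternatively, keep the mixed model but give all arms one common baseline mean.
- Report the adjusted 6-month between-arm differences as the primary effects, with the Holm-corrected contrasts applied to them.
- Include the baseline value of the outcome in the imputation model.

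No new data or assessments are needed, since every outcome is already measured at baseline. Recruitment has started, so the cost is a dated amendment, plus one degree of freedom per model. The sample size can stay as it is.

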### Study Design

This is an interventional, randomized controlled trial (RCT) with 3 parallel arms, including a nonblinded TAU group. The 2 experimental groups (EGpsych and EGcomp) complete 3 assessments: baseline prior to intervention start (T0), postintervention at week 12 (T1), and a 3-month postintervention follow-up, which represents the primary end point (6 mo after baseline, T2). In contrast, the TAU group follows an extended assessment schedule due to the 6-month waiting period: TAU participants complete a baseline measurement at study entry (T0), a second assessment following the 6-month waiting period and immediately before accessing the intervention (TAU-T1), a postintervention assessment after completing the 12-week program (TAU-T2), and a 3-month follow-up (TAU-T3). The 2 experimental groups receive access to the digital self-help program CHRONIC. Participants in the TAU group will receive access to the CHRONIC program with standardized computer-generated feedback (EGcomp version) after completing the 6-month waiting period. The 6-month waiting period for the TAU group was selected for 3 reasons. First, it reflects real-world access barriers in specialized pain services in Germany, where waiting times of 4 to 6 months are frequently reported for multidisciplinary pain treatment programs and specialist behavioral interventions, making this duration clinically realistic rather than arbitrary [3,23]. Second, extending the waiting period increases the likelihood of detecting natural symptom progression and pain chronification effects, allowing a meaningful comparison with the intervention arms and preventing artificially low variance caused by very short control periods. Third, choosing a 6-month window enables methodological alignment with the intervention design: since participants in the experimental arms undergo a 12-week treatment followed by a 3-month follow-up, the 6-month TAU period ensures comparable temporal exposure before receiving access to the program. The groups differ in the type of feedback received after each module: participants in the EGpsych receive individualized feedback written by the study team, whereas participants in the EGcomp receive standardized, template-based, computer-generated feedback. The study design is illustrated in Figure 1.

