Modules are time-locked to ensure standardized intervention exposure because the intervention is designed to run over a fixed 12-week period. Each new module becomes available exactly 7 days after the previous module has been released. Participants cannot access future modules ahead of schedule, and early progression or skipping forward is technically prevented. The program cannot be paused. All participants have a fixed consecutive 12-week access period, after which access to the intervention ends automatically. If participants choose not to complete a module in the week it becomes available, the next module is still released on schedule 7 days later. This allows participants to complete multiple outstanding modules in a shorter interval later on, reducing the time gaps between sessions while still operating within the fixed 12-week intervention window. All completion times and access patterns are recorded through backend timestamps and will be evaluated in adherence. To support structured engagement and continuity in self-monitoring, brief intersession assessments are implemented within the platform workflow. Before participants can begin the next module, they are required to complete a short check-in assessment referring to the preceding week, based on subscales derived from the West Haven-Yale Multidimensional Pain Inventory (WHYMPI; part 1 “Pain experience statements” and part 3 “Patient activity”). These assessments are integrated directly into the platform interface and are automatically presented at the start of each new session. The check-ins occur once per week, require approximately 2 minutes to complete, and refer to the participant’s experiences during the previous 7 days. Modules cannot be accessed until the corresponding check-in is completed, ensuring a consistent measurement structure across participants. There is no fixed time of day for completion since the brief assessment appears immediately when the new module is opened and remains available until submitted. These data are visualized in real time on the user’s personal dashboard as a line graph based on the summed scores to support self-monitoring. After each module, participants in the experimental groups receive motivational feedback—either individualized or computer-generated, depending on group assignment—delivered via the app and email shortly after session completion. Feedback is only triggered following the completion of a module. The feedback procedure differs between the 2 intervention conditions. In the EGpsych arm, feedback is written individually by psychologists from the study team. All potential feedback providers hold a university degree in psychology and have additional clinical experience in working with individuals with chronic pain. Feedback integrates participant-specific information derived from the weekly self-assessments. Messages are delivered asynchronously in written text format via the platform interface. In contrast, participants in the EGcomp arm receive standardized feedback messages prewritten by psychologists from the study team based on a fixed template system. These messages include the same structural components as in EGpsych (completion acknowledgment, motivational reinforcement, psychoeducational element, and goal reminder), but they do not integrate individual self-assessment data or module-specific personal content. The feedback is identical across all EGcomp participants and does not vary based on adherence patterns or timing. This standardized structure ensures consistency in length, tone, and delivery frequency across participants while maintaining methodological separation from tailored guidance. In both intervention arms, feedback messages are delivered asynchronously via the platform and email notification within 24 hours following module completion, and participants cannot respond to feedback in either condition. The feedback texts contain approximately 100 to 150 words per module. If participants complete multiple modules within a single day (catch-up use), EGpsych feedback is not provided separately for each module. Instead, one feedback message is provided referencing the last completed module and comparing the most recent assessment with the prior assessment, thereby reflecting the latest available change pattern rather than generating multiple module-specific feedback messages. Such accelerated completion patterns and potential overlaps in assessment windows are captured via timestamps and will be considered in adherence metrics and per-protocol (PP) definitions.

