
All analyses will be conducted according to both the intention-to-treat and PP principles. The intention-to-treat approach includes all randomized participants in the groups to which they were assigned, regardless of adherence to the intervention, thereby maintaining the benefits of randomization and reflecting real-world applicability. In contrast, PP analyses include only those participants who fully adhered to the intervention protocol, offering insights into the intervention’s efficacy under ideal conditions. Participants must complete at least 9 out of 12 modules (≥75%) within the intended 12-week intervention period to be included in the dataset. Participants below this threshold will be excluded from PP analyses. Comparing both approaches helps assess the robustness and generalizability of findings. Subgroup analyses may be conducted to explore whether intervention effects differ across specific participant characteristics, such as baseline pain severity, age, or gender. These analyses can help identify moderators of treatment effects and thereby contribute to a more personalized understanding of intervention efficacy. Moderator analyses will be exploratory in nature and interpreted with caution due to limited power. Adherence outcomes, including the number of completed modules, log-in frequency, and intervention dropout, will be compared descriptively and inferentially between EGpsych and EGcomp to evaluate potential differences in engagement patterns. Missing data will be handled using multiple imputation, which estimates missing values based on the observed data and includes random variation across imputations. This approach reduces bias and increases statistical power compared to complete case analyses, as it uses all available data while accounting for uncertainty introduced by the missingness [29].

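### The per-protocol rule (at least 9 of 12 modules) cannot be met by TAU before the 6-month comparison, so the per-protocol contrast of CHRONIC with TAU cannot support the robustness of the intention-to-treat result

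*Protocol article*

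**What the plan says.** Four statements in the protocol article bear on this point.

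- **Inclusion rule (Statistical Analysis).** "Participants must complete at least 9 out of 12 modules (≥75%) within the intended 12-week intervention period to be included in the dataset". The same section excludes "Participants who complete fewer than 9 modules or who finish all modules in an implausibly condensed time frame". It also describes the population in words: "PP analyses include only those participants who fully adhered to the intervention protocol". None of these sentences names an arm, and no separate criterion is given for TAU.
- **Scope (Statistical Analysis).** "All analyses will be conducted according to both the intention-to-treat and PP principles". This takes in the primary model, whose group factor has three levels including TAU and whose time factor is baseline versus the matched assessment at about 6 months.
- **Purpose (Statistical Analysis).** "Comparing both approaches helps assess the robustness and generalizability of findings".
- **TAU access (Study Design).** "Participants in the TAU group will receive access to the CHRONIC program with standardized computer-generated feedback (EGcomp version) after completing the 6-month waiting period". The TAU assessment used in the primary comparison, TAU-T1, is taken just before that access begins.

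**The concern.** The rule selects on behaviour that one of the three arms cannot show within the comparison window. The main question is CHRONIC versus TAU, and the plan intends to rerun that comparison in the PP set and set the result beside ITT. Depending on how the rule is applied to TAU, the rerun either has no control group or compares experimental participants chosen for finishing the program with controls who were not chosen in the same way. People who complete a 12-week self-help program may differ in motivation and course from those who stop. A PP result that matches or exceeds ITT could then arise from selection alone, yet be reported as support for the main finding.

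**Working it through.** The plan gives no figure for this point, so there is none to reproduce. The check is a count followed by an illustration.

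**Step 1: count TAU participants who qualify.** Modules available to TAU up to TAU-T1: 0 (Study Design). Modules required: 9 of 12 (Statistical Analysis). Since 0 < 9, no TAU participant meets the rule at the matched assessment. The PP version of the three-group model loses its TAU level and only EGpsych versus EGcomp remains.

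**Step 2: consider the other ways to treat TAU.**
- *Keep all TAU.* Controls are unselected, while the experimental arms are cut down by adherence after randomization.
- *Judge TAU on their own later 12-week access.* Controls are then selected on behaviour after their 6-month endpoint, under the EGcomp version of the program. The text does not describe this option, and it keeps outcome data collected after access out of the primary randomized comparison.

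Neither option gives groups that are comparable by randomization.

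**Step 3: illustrate the size when all TAU are kept.** Assumptions, none of them from the documents: there is no treatment effect; a share p of experimental participants reaches 9 modules; adherence propensity is normal and has correlation c with the improvement that would have occurred anyway. The mean shift in the adherers, in SD of change, is

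bias = c × φ(z) / p,

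where z is the cut-off that leaves the share p above it. For p = 0.6, φ(z) = 0.386 and φ(z)/p = 0.644; with c = 0.3 the bias is 0.3 × 0.644 = 0.193 SD.

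| Share p | φ(z)/p | c = 0.1 | c = 0.2 | c = 0.3 | c = 0.4 |
|---|---|---|---|---|---|
| 0.5 | 0.798 | 0.080 | 0.160 | 0.239 | 0.319 |
| 0.6 | 0.644 | 0.064 | 0.129 | 0.193 | 0.258 |
| 0.7 | 0.497 | 0.050 | 0.099 | 0.149 | 0.199 |
| 0.8 | 0.350 | 0.035 | 0.070 | 0.105 | 0.140 |

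The range is 0.035 to 0.319 SD. A negative c gives the same sizes in the opposite direction.

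**Step 4: translate into false-positive risk.** Assume equal allocation of the 200 participants (200/3, about 67 per arm; the article gives no ratio), no dropout and a two-sided 5% test. With p = 0.6 and c = 0.3, both experimental arms pooled give 133 × 0.6 = 79.8 adherers. The standard error is √(1/67 + 1/79.8) = 0.166, the bias is 0.193/0.166 = 1.17 standard errors, and the rejection rate is about 21%. Over p = 0.5 to 0.8 and c = 0.1 to 0.3, the rate is 5.4% to 20.5% for one experimental arm versus TAU and 5.6% to 28.2% for the pooled arms.

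**The case against.** **The rule was probably meant only for the program arms.** It speaks of intervention modules and an intervention period, adherence outcomes are compared only between EGpsych and EGcomp, and waiting without access is exactly what TAU was assigned to do. This is fair. A reader might infer that the PP set will certainly contain no TAU participants; that follows only from the literal wording. But the sensible reading, keeping all TAU, is the one that produces the selected-versus-unselected contrast. Nor is this merely a detail left to the SAP: the rule, its scope over all analyses and its role in judging robustness are all stated in the article.

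**The primary result is not at risk.** This stands. A reader might infer that randomization is broken for the main comparison. It is not: ITT keeps everyone as randomized, and the article itself credits ITT, not PP, with preserving randomization. No decision rule depends on PP.

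**The bias is assumed, not shown.** This also stands. The adherence shares and correlations are free inputs. People who improve early may stop, and those with persistent pain may continue, which would reverse the sign.

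**Condensed completion.** The article excludes from PP those who "finish all modules in an implausibly condensed time frame that violates the intended weekly structure will be excluded from the PP dataset", while its description of the application says of the release schedule: "This allows participants to complete multiple outstanding modules in a shorter interval later on". A reader might infer a contradiction, or a cut-off that can be chosen after results are seen. The documents do not support either. The application section says that accelerated patterns will be considered in the PP definitions, the Statistical Analysis section says full adherence is to be defined a priori, and a numeric cut-off is ordinary SAP content. The shorter restatement of the rule is an abbreviation. This is not part of the finding.

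**Conclusion.** The point holds for the PP comparison of CHRONIC with TAU. As written, the rule leaves no TAU participant. Under either workable alternative, the contrast is non-randomized and subject to selection bias of unknown size and direction. A spurious advantage for CHRONIC of about 0.04 to 0.32 SD is plausible if 50% to 80% of experimental participants reach 9 modules and adherence correlates 0.1 to 0.4 with untreated improvement. Those inputs are assumptions; the structural problem does not depend on them. Agreement between PP and ITT on this contrast should not be read as robustness. EGpsych versus EGcomp can still be run in the PP set, although it too is selected on behaviour after randomization.

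**What to change.** 1. State that the module-count criterion applies to EGpsych and EGcomp only, and label the PP comparison of those two arms descriptive.
2. Remove the claim that comparing PP with ITT assesses robustness where the contrast is CHRONIC versus TAU.
3. For that contrast, add a supplementary complier-average causal effect with randomization as the instrument, keeping all randomized participants. TAU has no access before TAU-T1, so non-compliance is one-sided and the estimate is straightforward to obtain.
4. Vary the threshold, from 9 modules down to any module use, and state the exclusion restriction as a limitation. Two features strain it. The program is described as cumulative, so benefit below 9 modules is likely. Allocation to TAU is unblinded and outcomes are self-reported, so assignment alone may shift responses. In its simplest form the estimate is the ITT effect divided by the adherent share. At an assumed 60% adherence it is the ITT effect divided by 0.6, or about 1.67 times as large, and this overstates the effect in compliers if partial users also benefit. That is why it should remain supplementary.

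The cost is a few sentences and one extra model, with an estimate that is less precise than ITT and relies on an added assumption. Primary endpoint collection is expected to run to January 2027, so the wording can be settled before analysis.
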